### Statistical analysis

To address whether the 6-month multi-domain exercise program affects working memory or episodic memory performance and brain functioning, we will employ a two-way repeated-measure analysis of variances (ANOVA) of mixed design with group status (i.e., multi-domain exercise group vs. control group) as the between-subject variable and time points (i.e., Baseline-Assessment vs. Post-Assessment) as the within-subject variable, with the Greenhouse–Geisser correction, where deemed appropriate. The two-way ANOVA will be employed individually for each primary outcome. Multiple *t*-test comparisons will be conducted as follow-up by setting the familywise alpha levels at 0.05, prior to a Bonferroni correction.

To address the moderating role of *ApoE* genotype on the effect of the multi-domain exercise program on working memory and episodic memory performance, as well as brain function assessed from neuroimaging metrics, we will employ the three-way repeated-measure ANOVA of mixed design with group status as the between-subject variable, and *ApoE* genotype [i.e., high-risk candidates (*ApoE* ε3/ε4 and *ApoE* ε4/ε4) vs. the low-risk candidates (*ApoE* ε2/ε4, *ApoE* ε2/ε3, *ApoE* ε2/ε2, and *ApoE* ε3/ε3)] and time points as the within-subject variable, with a Greenhouse–Geisser correction where deemed appropriate. In addition, multiple *t*-test comparisons will be conducted as follow-ups by setting the familywise alpha levels at 0.05 prior to a Bonferroni correction.

To address whether the effects of the multi-domain exercise program on working memory, episodic memory, and brain function are mediated by physical fitness and BDNF, we will employ Pearson product-moment correlations to examine relationships between change in physical fitness, BDNF, and the primary and secondary outcomes. Separate mediation analyses will be conducted using PROCESS software for SPSS. Statistical significance of mediators will be considered if the 95% bias-corrected bootstrap confidence interval (5,000 bootstrap samples) does not include zero. For all analyses, age, sex, BMI, and educational levels will be controlled for, and the alpha value will be set at 0.05, prior to statistical adjustment for all analyses.

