## Methods

### Study design and schedule

The multi-domain interventional trial of WE-BFit is designed as a double-arm, randomized controlled trial (RCT) targeting potential factors for promoting working memory, episodic memory, and brain function in cognitively healthy late middle-aged and older adults who are and who are not at genetic risk for AD. The trial is planned to start in April 2022 and aims to recruit 100 eligible participants who will be randomly assigned into two parallel groups (i.e., the multi-domain exercise group, *n* = 50; the control group, *n* = 50). *ApoE* genotypes of eligible participants will be examined at the baseline assessment. Additionally, other primary outcomes (i.e., working memory, episodic memory, and brain function) and secondary outcomes (i.e., multiple components of physical fitness and BDNF) will be assessed before and after the 6-month intervention. This trial will be led primarily by the Faculty of Physical Education and Sport Sciences of the National Taiwan Normal University. A flow chart of the current trial is presented in Figure 2.

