### Power analysis

The study will recruit a total sample size of 100 participants for final statistical analyses. The sample size is estimated from an *a priori* power analysis using G^*^Power 3.1.9.4 (power = 0.80, alpha = 0.05) and the effect size (Hedges' *g* = 0.30) based upon our previous meta-analysis that examines the effects of exercise interventions on executive function, including working memory in adults of age 55–65 years (Chen et al., 2020a).

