Several challenges of this study are worth mentioning. For instance, the current trial will recruit 50 cognitively healthy participants with a genetic risk for AD. Nevertheless, the recruitment of sufficient participants is challenging, given that the prevalence of *ApoE* ε4 allele(s) in Taiwan is only around 20% (Hong et al., 1996; Wang et al., 2011). Unfortunately, this challenge will be further escalated by the occurrence of the COVID-19 pandemic. Although this challenge might be partially alleviated through recruiting *ApoE* ε4 allele(s) carriers from our previous research and the progressive ease of the COVID-19 pandemic in Taiwan, we still expect the inclusion of a sufficient number of participants, especially the *ApoE* ε4 allele(s) carriers, will be difficult. Drop-out and adherence will be other challenges in the current study. Two strategies will be applied to curtail these challenges. First, frequent contacts and regular newsletters will be delivered to all participants from the research group. Furthermore, the multi-domain exercise group can attend two out of 10 optional exercise sessions each week instead of adhering to a fixed exercise schedule. These approaches enhance the personal connection to the study and provide user-friendly access to the exercise program, and we expect this to enhance participants' adherence and minimize the risk of them withdrawing from the intervention (Robiner, 2005). Finally, the current trial collects a considerable amount of outcome measures, and many of them have to be collected in a time-sensitive manner. For instance, to accurately reflect the relationships between physiological conditions and brain health, physical fitness, BDNF levels, cognitive tasks, and fMRI assessments will be completed within 3 weeks before and after the 6-month exercise program, respectively. To overcome this potential challenge, a limited number of participants (e.g., five people) will be grouped as one intervention unit, and the unit will coordinate the most suitable time for initiating the assessments and exercise program.

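### The primary group-by-time ANOVA is a change-score test that leaves out the baseline score; adjusting for baseline would be more precise with no extra data

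*Protocol article*

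**What the plan says.** The Statistical analysis section of the protocol article fixes the primary model: "we will employ a two-way repeated-measure analysis of variances (ANOVA) of mixed design with group status" as the between-subject factor and "time points (i.e., Baseline-Assessment vs. Post-Assessment) as the within-subject variable". It adds that "The two-way ANOVA will be employed individually for each primary outcome". The covariates are also fixed: "For all analyses, age, sex, BMI, and educational levels will be controlled for". The baseline value of the outcome enters only as one level of the time factor.

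Study design and schedule says that the primary outcomes "will be assessed before and after the 6-month intervention", so each participant has at most one baseline and one post score per outcome. Randomization and blinding stratifies by ApoE risk group only. The Discussion concedes that "Drop-out and adherence will be other challenges in the current study".

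Power analysis gives "power = 0.80, alpha = 0.05", a Hedges' g of 0.30 and a total of 100 participants. The Participants section names the G*Power routine for a repeated-measures within-between interaction.

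**The concern.** With two arms and two time points, the group-by-time interaction compares mean change between arms and does nothing else. The Greenhouse-Geisser correction has no effect with only two levels of time. Adding age, sex, BMI and education turns the test into a regression of change on group and those four variables.

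A change score fixes the coefficient of baseline at 1. Under randomisation, with equal variances at the two times, the best coefficient is rho, the baseline-post correlation. Any gap between 1 and rho is avoidable noise. It also leaves the estimate exposed to chance baseline differences, because stratification does not balance baseline memory scores.

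At stake is precision in a trial of 100 whose authors expect recruitment to be difficult. There is a second, conditional risk: if the link between baseline performance and dropout differs between the exercise and control arms, complete-case change scores are biased and a baseline-adjusted analysis need not be.

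**Working it through.** **Inputs from the article.** Two arms, 1:1, N = 100 (50 per arm); alpha 0.05, taken as two-sided because the F test is non-directional; power 0.80; g = 0.30; one baseline and one post score.

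**Assumed.** rho is not stated, so 0.3 to 0.9 is shown. The outcome SD is taken as 1 at both times.

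**Step 1: the plan's own sample size.** For the within-between interaction, lambda = f² × N × 2/(1 − rho), with 1 and N − 2 degrees of freedom. With f = g/2 = 0.15 and rho = 0.5, 80% power needs N = 90, and power at N = 100 is 84.4%. The stated 100 follows if an unstated 10% dropout is added (90/0.9 = 100), or approximately with rho near 0.45 (N = 98). The figure can therefore be reached, but only with inputs that the article does not give.

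On this scale, lambda at N = 100 is 0.0225 × 100 × 2/0.5 = 9. The change-score test has noncentrality d² × 25/[2(1 − rho)] = 25d² at rho 0.5, so this planning scale corresponds to a 0.6 SD difference in change.

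**Step 2: the equivalence.** On one simulated trial the interaction F and the squared change-score t were both 3.72185.

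**Step 3: variance without other covariates.**
- Change score: 2(1 − rho)
- Baseline-adjusted: 1 − rho²
- Ratio: (1 − rho²)/[2(1 − rho)] = (1 + rho)/2

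Power is from the noncentral t with 50 per arm. The ANCOVA variance is inflated by 1 + 1/96 for the estimated slope and has 97 rather than 98 degrees of freedom.

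| rho | variance ratio | CI narrower by | power, 0.30 SD: change → ANCOVA | power, 0.60 SD: change → ANCOVA |
|---|---|---|---|---|
| 0.3 | 0.65 | 19% | 0.24 → 0.34 | 0.71 → 0.87 |
| 0.5 | 0.75 | 13% | 0.32 → 0.40 | 0.84 → 0.93 |
| 0.7 | 0.85 | 8% | 0.48 → 0.54 | 0.97 → 0.99 |
| 0.9 | 0.95 | 2.5% | 0.91 → 0.92 | 1.00 → 1.00 |

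After the slope inflation, the ratio reaches 1 only at rho of about 0.98.

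**Step 4: variance with the planned kind of covariates.** The plan already adjusts for four variables, which absorb some of the same variance. In 4,000 simulated trials of 100, four covariates were in both models and together explained 20% of baseline variance (an assumption). The ratios were 0.70, 0.79, 0.89 and 0.96 at rho 0.3, 0.5, 0.7 and 0.9. A closed form agrees closely: (1 + rho)/[(1 + rho) + 0.8(1 − rho)], for example 1.5/1.9 = 0.79 at rho 0.5. In participants, 1/0.79 = 1.27 and 1/0.89 = 1.12, so the gain is worth about 27% more at rho 0.5 and 12% more at rho 0.7. Both estimators averaged 0.29 to 0.30 for a true 0.30.

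**Step 5: dropout.** If dropout depends only on baseline within each arm, the complete-case change-score estimate is the true effect minus (1 − rho) × D. D is the difference in mean baseline, exercise minus control, among completers, in SD units.
- Same dependence in both arms: D = 0, and the estimate stays at 0.30 for a true 0.30.
- Dependence in the exercise arm only, with low scorers leaving more often and about 18 to 19% dropout in each arm (assumed): D is about 0.17. The estimate is 0.30 − 0.5 × 0.17 = 0.215 at rho 0.5 and 0.30 − 0.3 × 0.17 = 0.249 at rho 0.7. Simulation gave 0.215 and 0.249.
- Complete-case ANCOVA in the same simulated data returned 0.30.

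**The case against.** The strongest defence is that the planned test is legitimate. Randomisation makes the change-score contrast unbiased, so the loss is one of efficiency. That stands. So does the point that the gain depends on an unstated rho: at 0.9 it is negligible, and the covariates already in the plan reduce it somewhat.

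A reader might go on to infer four stronger criticisms. The document does not support them.

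- *Dropping non-completers biases the ANOVA.* Dropout that depends on baseline in the same way in both arms leaves the change-score estimate unbiased (Step 5). Bias needs a dependence that differs by arm. ANCOVA also excludes anyone without a post score, so exclusion as such is not the fault.
- *Chance baseline imbalance makes the result biased.* Over repeated randomisations it does not. It is the same precision loss seen conditionally.
- *The trial is underpowered.* That depends on how g is read. At rho 0.5, power at N = 100 is 0.32 for a 0.30 SD difference but 0.84 on the G*Power scale with f = 0.15. This is a separate sample-size question, and the present point holds on either reading.
- *Efficacy may be claimed from within-group t-tests.* The article calls these tests follow-ups with a Bonferroni correction, and it sizes the trial on the within-between interaction. Nothing in it rests efficacy on within-group change.

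Detailed missing-data handling may sit in a fuller document and is not criticised here.

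**Conclusion.** The point holds as one of efficiency. The article fixes a covariate-adjusted change-score test and a covariate list that omits the baseline score, although that score is collected in any case. Adjusting for it reduces the variance of the treatment effect to about 0.79 of its planned value at rho 0.5 and 0.89 at rho 0.7, with a range of 0.70 to 0.96 over rho 0.3 to 0.9. These figures assume equal variances at the two times and covariates explaining 20% of baseline variance. Protection against arm-specific, baseline-dependent dropout is a further benefit. Its size rests on an assumed mechanism, and the article gives no dropout rate. The change is worth making, but the planned analysis is not invalid.

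**What to change.** For each primary outcome, replace the two-way ANOVA with an ANCOVA of the post score on group, adjusting for the baseline score of that outcome, ApoE risk stratum (the randomisation factor), age, sex, BMI and education. Report the adjusted between-group difference with its 95% CI as the efficacy result.

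A longitudinal mixed model with a common baseline mean for the two arms is an alternative. It also keeps participants who have only a baseline score, which ANCOVA does not.

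The cost is about two degrees of freedom, one for the baseline slope and one for the ApoE stratum. No visit or measurement is added. The Power analysis text should name the new model and state the assumed rho. The ApoE-moderation analysis should take the same form, with a group-by-ApoE term in the baseline-adjusted model. For imaging outcomes, the same covariates need to be set up in whichever software analyses them. The wording should be changed before any unblinded analysis.

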### Participants

To ensure a sufficient sample size, the sample size calculation for the current study was conducted using G^*^Power version 3.1.9.4 (ANOVA; repeated measures, within-between interaction). Multiple recruitment strategies will be utilized, including online social media advertising and word-of-mouth referrals, as well as posters and flyers placed or distributed in local community centers and organizations. Finally, individuals from previous studies will also be screened for recruiting potential participants. Before participating in the current study, potential participants will be screened by phone, followed by an on-site interview to ensure they meet the inclusion criteria.

Eligible participants (half of them are *ApoE* ε3/ε4 or *ApoE* ε4/ε4 carriers) will be provided sufficient information, and informed consent relating to the study will be provided prior to the initiation of the study. Recruitment, enrollment, and randomization will occur on a rolling basis. Finally, a total of 100 community-dwelling, cognitively healthy adults aged 45–70 years who are able to participate in moderate-intensity exercise will be recruited in a 1-year time period in Taipei, Taiwan. The inclusion and exclusion criteria are detailed in Table 1.

**Table 1 T1:** Inclusion and exclusion criteria for participating in the study.

**Inclusion criteria**	**Exclusion criteria**
- Adults aged from 45 to 70 years	- Diagnosed or self-reported cognitive problems (e.g., mild cognitive impairment or dementia)
- Normal or corrected-to-normal vision	- The diagnosed or self-reported physical disease (e.g., untreated hypertension and chronic heart disease, stroke, brain tumor, musculoskeletal disorders, other exercise contradictions)
- Able to speak and read Chinese	- Diagnosed or self-reported major psychiatric illness (e.g., major depression, schizophrenia)
- Scores of MMSE ≥ 25	- Diagnosed or self-reported neurodegenerative disease (e.g., AD and other dementias, PD and PD-related disorders, Huntington's disease)
- PAR-Q score = 0	- History of severe alcohol or drug abuse
- Able to conduct the exercise with moderate intensity	- History of chemotherapy
- Meet the criteria to undergo MRI	- Unable to complete the MRI scan
	- Traveling consecutively for 3 weeks or more during the study
	- Unwillingness to be randomized to one of the two groups
	- Currently participating in another study trial

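### Follow-up t-tests after a 2 x 2 group-by-time ANOVA add nothing needed to locate the effect, and the plan does not name the between-arm contrast as the test that decides efficacy

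*Protocol article*

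**What the plan says.** The Statistical analysis section plans a "two-way repeated-measure analysis of variances (ANOVA) of mixed design with group status (i.e., multi-domain exercise group vs. control group) as the between-subject variable", with "time points (i.e., Baseline-Assessment vs. Post-Assessment) as the within-subject variable". It adds: "The two-way ANOVA will be employed individually for each primary outcome". The follow-up is then fixed: "Multiple *t*-test comparisons will be conducted as follow-up by setting the familywise alpha levels at 0.05, prior to a Bonferroni correction". Nearly the same sentence follows the three-way ApoE model. The section does not list the contrasts to be tested. It does not make them depend on any ANOVA result, and it does not say which term (group, time or their interaction) answers the efficacy question.

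The Participants section gives the sample-size procedure as "ANOVA; repeated measures, within-between interaction". The trial is therefore sized on the interaction, but the analysis text does not carry that forward as the deciding test.

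**The concern.** Follow-up tests are useful when an omnibus test has several degrees of freedom and one must find where the difference lies. Here the interaction has one degree of freedom and is itself the between-arm difference in change. Four pairwise cell comparisons remain:

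- the pre-post change in the exercise arm;
- the pre-post change in the control arm;
- the arms compared at baseline;
- the arms compared at post-assessment.

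The first three do not test the treatment effect. The fourth does, because allocation is randomised, but it ignores the baseline value.

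Both arms perform the n-back and RISE tasks before and after the intervention, so a gain from practice in both arms is plausible. A significant change in one arm beside a non-significant change in the other can then look like a treatment effect when the arms do not differ. Bonferroni does not address this: it controls how many tests are run, not which question each one answers.

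**Working it through.** **Inputs.** From the protocol: 2 arms, 2 times, 50 per arm, alpha 0.05. Assumed, because the protocol does not state them: an equal gain in both arms of 0.2 to 0.4 SD; a pre-post correlation r of 0.5 or 0.7; and a Bonferroni divisor of 4 (the four comparisons above), giving 0.0125. Covariates are ignored.

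**1. The plan's own figure.** The Power analysis section gives N = 100 for 80% power from "the effect size (Hedges' *g* = 0.30) based upon our previous meta-analysis". With the noncentral F for the within-between interaction, lambda = f² x N x 2 / (1 - r), and f = g/2 = 0.15 (an assumed conversion), the required N is 90 at r = 0.5, 98 at r = 0.45 and 108 at r = 0.4. Since r is not stated, 100 is attainable but cannot be confirmed. The point does not depend on it.

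**2. The interaction is the change-score test.** The contrast is (E1 - E0) - (C1 - C0), where E and C are the exercise and control means and 0 and 1 are baseline and post. Its F on 1 and 98 df equals the square of the independent t-test on change scores. On one simulated data set both gave 10.3156.

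**3. How often only the exercise arm is significant when there is no treatment effect.** Let p be the power of a paired t-test with n = 50, df = 49 and noncentrality d x sqrt(50), where d is the gain in SD of change. The arms are independent, so the probability is p(1 - p).

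| d | p at 0.05 | p(1 - p) | p at 0.0125 | p(1 - p) |
|---|---|---|---|---|
| 0.2 | 0.283 | 20% | 0.130 | 11% |
| 0.3 | 0.548 | 25% | 0.329 | 22% |
| 0.4 | 0.792 | 16% | 0.595 | 24% |

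The range is 11% to 25%.

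A simulation (20,000 trials per setting, follow-ups at 0.0125, gain in outcome SD) agrees. It gave 11%, 23% and 24% at r = 0.5, where the SD of change equals the outcome SD, and 17%, 25% and 13% at r = 0.7. In the same trials:

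- The interaction was significant in 4.8% to 5.2%, counting both directions.
- With a gain of 0.3 SD, the exercise arm improved significantly while the interaction did not reach 0.05 in 31% (r = 0.5) or 54% (r = 0.7).
- If follow-ups were read only after a significant interaction, the exercise-only pattern appeared in about 2%.

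**4. Efficiency of the three between-arm tests.** For a between-arm effect of 0.3 outcome SD with 50 per arm, noncentrality = (0.3 / s) x sqrt(50/2) = 1.5 / s:

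| Test | s | Power, r = 0.5 | Power, r = 0.7 |
|---|---|---|---|
| Post-assessment only | 1 | 32% | 32% |
| Change (interaction) | sqrt(2(1 - r)) = 1.000; 0.775 | 32% | 48% |
| Baseline-adjusted | sqrt(1 - r²) = 0.866; 0.714 | 40% | 55% |

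These powers only rank the three tests and should not be set against the planned 80%. At r = 0.5 and N = 100, f = 0.15 gives lambda = 0.0225 x 100 x 2 / 0.5 = 9, while a 0.3 SD difference in change gives 1.5² = 2.25. Step 1 therefore uses a different effect scale.

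**The case against.** The other side has real points.

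- A reader might infer that the plan will claim efficacy from within-arm p-values. It says no such thing. The ANOVA is presented as the method that answers the efficacy question, the t-tests are called follow-up and are Bonferroni-corrected, and the sample size rests on the interaction.
- A reader might infer that a time effect alone would set off the t-tests. No trigger is stated, so that rule cannot be attributed to the plan. Under the ordinary sense of follow-up, read after a significant interaction, the misleading pattern falls to about 2%.
- A reader might infer that every possible follow-up fails to test the treatment effect. That is wrong. The post-assessment between-arm test is a valid randomised comparison (simulated type I error 4.6% to 5.3%), and a t-test on change scores simply repeats the interaction.
- A reader might put the misleading pattern near one half by taking 2p(1 - p). That also counts trials in which only controls improve, which would not support the exercise programme.
- The choice of contrasts and any gating are often left to a SAP, which may exist.

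The last point does not dispose of the matter. Running multiple t-tests after a 2 x 2 model is a stated choice, not an omission, and it is a poor one whatever a SAP adds. The remaining points limit the size and wording of the concern and are accepted here.

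**Conclusion.** The concern holds in limited form. The section commits to follow-up t-tests that a 2 x 2 design does not need. It does not name the between-arm contrast as decisive, although the sample size is built on it. The within-arm and baseline tests carry no information on the treatment effect, and the post-assessment test is valid but less efficient than a baseline-adjusted one (32% against 40% or 55% power for 0.3 SD).

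If the within-arm results were read on their own, a pattern favouring exercise would arise in 11% to 25% of trials with no effect, against 5% for the between-arm test. That range rests on an equal gain of 0.2 to 0.4 SD in both arms and on a reader who sets the interaction aside; neither is in the protocol. This is a gap in how the conclusion is protected, not evidence that a wrong conclusion is planned.

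**What to change.** For each primary outcome, state that the sole efficacy test is the between-arm difference at post-assessment, adjusted for the baseline value and the covariates already listed, reported with its 95% CI. Delete the follow-up t-tests for the two-way model, or report within-arm changes descriptively without p-values. For the ApoE model, replace the unspecified t-tests with the between-arm difference and CI within each genotype stratum.

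The baseline values are already collected, so the change needs no new data or visits and involves fewer tests. At the assumed correlations, baseline adjustment raises power for a 0.3 SD effect from 32% to 40% (r = 0.5) or from 48% to 55% (r = 0.7) relative to the interaction test. The cost is revised analysis wording and the loss of within-arm p-values.

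### The Pearson correlations offered towards the mediation question cannot carry the plan's own covariates and contain no term for treatment arm; the effect is modest and confined to these supporting correlations

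*Protocol article*

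**What the plan says.** All the relevant text is in the Statistical analysis section of the protocol article, in the paragraph on mediation.

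- The paragraph opens with its question: "To address whether the effects of the multi-domain exercise program on working memory, episodic memory, and brain function are mediated by physical fitness and BDNF".
- The first method named for that question is correlation: "we will employ Pearson product-moment correlations to examine relationships between change in physical fitness, BDNF, and the primary and secondary outcomes".
- A second, distinct method follows: "Separate mediation analyses will be conducted using PROCESS software for SPSS".
- The criterion for a mediator belongs to that second method: "Statistical significance of mediators will be considered if the 95% bias-corrected bootstrap confidence interval (5,000 bootstrap samples) does not include zero".
- The paragraph ends with a general rule: "For all analyses, age, sex, BMI, and educational levels will be controlled for, and the alpha value will be set at 0.05".

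Nothing there says whether the correlations use all participants together, each arm separately, or an adjustment for arm. The PROCESS model number and independent variable are not given either.

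**The concern.** Two things are wrong with the correlation step as named.

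First, the section contradicts itself. A Pearson product-moment correlation relates two variables and has no place for covariates, yet the closing rule requires four covariates in every analysis. The named method cannot satisfy the rule.

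Second, arm is absent both from the correlation and from the covariate list. The trial expects the programme to change fitness, BDNF and memory. If the two arms are put into one correlation, participants in the exercise arm tend to sit high on both axes and controls low on both. That alone yields a positive correlation, even if those whose fitness improved most are no more likely than others in their arm to have improved in memory. Such a correlation would restate that both variables differ by arm, and a reader could take it as a sign that one change explains the other. The distortion is largest when the intervention works.

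**Working it through.** **The plan's own figures.** No figure is given for the correlation or mediation analyses. The only stated size is 100 participants (Power analysis: power 0.80, alpha 0.05, Hedges' g = 0.30; the Participants section names the G*Power within-between interaction routine). With f = g/2 = 0.15, that routine gives N = 90 if the correlation between time points is 0.5, N = 98 at 0.45 and N = 108 at 0.4. The article does not state this correlation, so 100 can be neither confirmed nor refuted. The present point does not depend on it.

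**Inputs.**
- 50 per arm: 100 participants (Power analysis), 1:1 allocation (Randomization and blinding).
- Arm effect on memory change, d2: 0.30 from the Power analysis, read in SD of change. If g is instead in raw-score SD, d2 = 0.30/√(2(1−ρ)), where ρ is the correlation between time points. That gives 0.27 at ρ = 0.4, 0.30 at 0.5 and 0.42 at 0.75.
- Arm effect on mediator change, d1: not stated. Assumed range 0.3 to 0.8 SD of change, with 1.5 as an extreme.
- Within-arm association between mediator change and memory change: set to zero, to isolate what arm alone does.

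**Induced correlation.** Code arm as 0/1 with half in each group, so its variance is 1/4. Within-arm SDs are 1. Then the covariance is d1·d2/4, the variances are 1 + d1²/4 and 1 + d2²/4, and

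r = (d1·d2/4) / √[(1 + d1²/4)(1 + d2²/4)].

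For d1 = 0.8, d2 = 0.3: 0.06 / √(1.16 × 1.0225) = 0.06/1.089 = 0.055.

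**Rejection rates.** 40,000 simulated trials per row, 50 per arm, two-sided 5% test of zero correlation:

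| d1 (mediator) | d2 (memory) | induced r | pooled Pearson rejects | adjusted for arm rejects |
|---|---|---|---|---|
| 0 | 0.3 | 0 | 5.2% | 5.1% |
| 0.3 | 0.3 | 0.022 | 5.6% | 5.0% |
| 0.5 | 0.3 | 0.036 | 6.5% | 4.8% |
| 0.8 | 0.3 | 0.055 | 8.8% | 5.0% |
| 1.5 | 0.3 | 0.089 | 14.4% | 5.0% |
| 0.8 | 0.5 | 0.090 | 14.5% | 4.9% |
| 0.8 | 0.8 | 0.138 | 28.1% | 4.8% |
| 1.5 | 0.8 | 0.223 | 62.5% | 5.0% |

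The rows with d2 = 0.3 use the planned memory effect. The last three go beyond it. Adjusting for arm restores about 5% throughout.

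**Does the artefact reach the mediation test?** A bias-corrected bootstrap of the indirect effect was simulated with arm as the independent variable, the mediator-to-memory path adjusted for arm, and a true value of zero on that path (1,500 trials, 2,000 resamples; the plan uses 5,000). It excluded zero in 2.7% to 8.7% of trials. Raising d2 from 0.3 to 0.8 did not raise the rate: 8.7% to 6.8% at d1 = 0.8, and 6.7% to 6.5% at d1 = 1.5. The pooled Pearson test went from 8.8% to 28.1% and from 14.4% to 62.5% over the same steps.

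**The case against.** The strongest reply has four parts.

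*Pooling is not in the text.* This is correct. The article is silent on arm, and a condensed article may leave such detail to a fuller plan. Pooling is the plain reading of an unqualified correlation in a two-arm trial, but it is an inference, and the arm part of this point is conditional on it. The covariate contradiction is not: both halves are printed in the same paragraph.

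*The covariate rule may be shorthand that turns the correlation into a partial one.* This is possible, since a partial correlation is a product-moment correlation of residuals. Even so, the rule lists only age, sex, BMI and education, so that reading would still leave arm out.

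*The correlations do not decide mediation.* This stands, and it limits the point. A reader might infer that the trial's mediation conclusion is itself biased. The document does not support that: it ties a mediator's significance to the bootstrap interval from PROCESS, and a simple mediation model with arm as the independent variable adjusts the mediator-to-outcome path for arm.

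*Rejection is not a false positive for the pooled quantity.* This is also true. When arm shifts both variables, the pooled population correlation really is non-zero. The rejection is misleading only as evidence of a link within arms, which is the link that matters for mediation.

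A reader might also infer that the matrix is circular, because the correlations extend to the secondary outcomes and the Study design and schedule section defines these as "secondary outcomes (i.e., multiple components of physical fitness and BDNF". That is a minor matter. Fitness change against BDNF change is a legitimate pair, and only a measure paired with itself is empty.

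**Conclusion.** The point holds in limited form. The named method cannot meet the plan's own covariate rule, and this rests on the text alone. The method also has no term for arm. If the arms are pooled, an arm effect on both variables produces an association with none within arms.

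At the planned memory effect of 0.30 the size is modest: r of about 0.02 to 0.06 and rejection of 5.6% to 8.8%, for assumed mediator effects of 0.3 to 0.8. It is nil if the programme does not move the mediator, and it becomes large only if both effects are well above these values. The figures assume 50 complete participants per arm, normally distributed changes and a memory effect expressed in SD of change. The supporting correlations are affected. The group-by-time analyses of the primary outcomes and the PROCESS criterion are not.

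**What to change.** In the mediation paragraph, replace the Pearson correlations with partial correlations, or regressions of outcome change on mediator change, adjusted for treatment arm, age, sex, BMI and education. Label them descriptive. State that the mediation conclusion rests on the PROCESS indirect effect, with arm as the independent variable.

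The cost is a sentence or two of text and no new data. The reported correlations may come out slightly smaller.
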